## 7    **Abstract**

8

## 9    **Background**

10   Preterm newborns receiving placental transfusion at birth have better neonatal outcomes,  
11   particularly a decrease of hospital mortality. Placental transfusion strategies performed in preterm  
12   babies at delivery have been delayed cord clamping and cord milking. However, both these  
13   strategies did not explore the contribution of the start of breathing during placental transfusion,  
14   because they are performed in a short time frame (30-60 sec for delayed clamping and <20 sec  
15   for cord milking). Thus, newborn bedside assistance near to the delivering mother, leaving the  
16   cord unclamped, would allow to evaluate the possible beneficial effects of prolonged transfusion  
17   strategy associated to newborns' breathing, both spontaneously started or artificially supported  
18   during initial steps of stabilization, on early infant postnatal adaptation and outcomes.

19

## 20   **Study Design**

21   We present the design of a randomized, multicenter, controlled study, whose aim is to assess the  
22   effectiveness of delivery room assistance with intact placental circulation in comparison to cord  
23   milking for improving outcomes in very preterm newborns. A total of 212 infants born at 23+0 to  
24   29+6 weeks of gestational age will be enrolled and randomized to receive assistance with intact  
25   placental circulation or cord milking at birth.

26   The primary outcome of the study is the comparison between groups of the risk of developing the  
27   composite outcome of grade 3-4 intraventricular hemorrhage (3-4 IVH), bronchopulmonary  
28   dysplasia (BPD) and mortality. Secondary outcomes include the comparison between groups of  
29   the need and duration of respiratory support, hemodynamic parameters and cerebral  
30   oxygenation, need and number of blood transfusions and inotropic drugs use in the first 24 hours.

31

## 32   **Discussion**

33   The results of this study will provide new information about the effectiveness of assistance with  
34   the placental circulation intact for improving outcomes in the neonatal period of preterm babies.  
35   Delaying cord clamping at 3 minutes of life while starting ventilation assistance (if needed) of the  
36   baby could permit to evaluate the contribution of the start of an efficacious breathing  
37   (spontaneous or assisted) before clamping on the early postnatal adaptation and outcomes in the  
38   neonatal period.

39

40   **Keywords:** randomised trial, preterm birth, delayed cord clamping, neonatal care at the bedside,  
41   cord milking, neonatal resuscitation

42

43   Trial Registration: Clinicaltrials.gov NCT02671305 (date of registration: 26 JAN 2016)

44 <https://clinicaltrials.gov/show/NCT02671305>

45

## 46 **INTRODUCTION**

47 Leaving the cord unclamped during the first minutes of life determines a net passage of 25 to 40  
48 ml/kg of blood from the placenta to the newborn depending on gestational age, timing of cord  
49 clamping, postnatal infant position, onset of breathing, and administration of uterotonics to the  
50 mother (1). Placental transfusion (PT) seems to play an important role in the respiratory and  
51 hemodynamic adaptation of the newborn during the transition phase (2). In fetal life, oxygenated  
52 blood coming from the placenta reaches the heart left ventricle through the umbilical vein and  
53 foramen ovale (3). Therefore, the unphysiological immediate clamping of the cord at birth  
54 determines an abrupt and prolonged reduction of the left ventricle preload, which will be  
55 maintained till an optimal blood return from the lungs through pulmonary veins will occur. The  
56 onset of spontaneous or assisted newborn's lung ventilation increases pulmonary blood flow and  
57 venous return to left ventricle, thus restoring more or less rapidly the left ventricle preload. These  
58 early major fluctuations of the cardiac output (abruptly decreased and then increased again) are  
59 associated with fluctuations of cerebral blood flow and pressures in animals (4). Instead, a  
60 physiological-based cord clamping, that is delaying cord clamping till after the animal/newborn's  
61 breathing, has not been associated with such hemodynamic fluctuations, thus potentially  
62 preventing cerebral vasculature rupture (5) and reducing the risk of critical neonatal outcomes  
63 (6).

64 However, very preterm infants only briefly (30-60 sec) delayed cord clamped, as in the majority of  
65 published trials, might not receive the best benefits from the procedure, as a time period equal or  
66 less than 1 minute of life is too short to obtain an optimal ventilation of the lungs. On the basis of  
67 these considerations, we hypothesized that neonatal assistance in the delivery room during a  
68 prolonged placental circulation intact (PCI) allows a better postnatal adaptation and improves  
69 outcome in preterm infants <30 weeks gestation.

70 Cord milking (UCM), that is pinching the cord close to the mother and running the fingers towards  
71 the infant at a speed of 10cm/sec, usually repeated 3 to 5 times, is an unphysiological procedure  
72 able to rapidly (usually within 20 sec of life) deliver a PT at birth. However, little is known about  
73 the acute physiological effects of UCM and how it influences the cardiovascular transition after  
74 birth. UCM could potentially determine harmful hemodynamic changes similar to those occurring  
75 after immediate cord clamping at birth. To date, all published studies demonstrate that UCM may  
76 have some advantages over immediate cord clamping at birth, such as lower risk for oxygen  
77 requirement at 36 weeks and IVH of all grades, and over short delayed cord clamping, such as  
78 higher initial Hb, higher blood pressure, and improved systemic blood flow and urine output for  
79 infants delivered by cesarean section (7-8).

80 The present study has been designed to assess the effectiveness of assistance with PCI  
81 clamping cord at 3 min of life in comparison with UCM for improving outcome in preterm infants.  
82

## 83 **STUDY DESIGN AND POPULATION**

### 84 **Study design**

85 This is a randomized, open-label, parallel-group, multicenter, prospective clinical trial, involving  
86 eight Neonatal Intensive Care Units (NICUs) in Italy. The trial was designed following the SPIRIT  
87 2013 statement (see populated SPIRIT checklist provided as an Additional file). Patients who  
88 meet inclusion criteria will receive a bedside assistance with PCI immediately after birth and  
89 during the first 3 min of life or cord UCM (milking four times 20 cm of cord) followed by cord  
90 clamping within 20 sec of life.  
91

### 92 **Study population**

93 The study is carried out in eight Italian NICUs. The participating centers are listed below:

- 94 - Neonatal intensive Care Unit, Division of Neonatology, Careggi University Hospital of Florence,  
95 Firenze, Italy
- 96 - Neonatal Intensive Care Unit, Division of Neonatology, Fondazione IRCCS “Ca’ Granda”  
97 University Hospital, Milano, Italy
- 98 - Neonatal Intensive Care Unit, “Maggiore” Children Hospital of Bologna, Bologna, Italy
- 99 - Neonatal Intensive Care Unit, Division of Neonatology, “Infermi” Hospital, Rimini, Italy
- 100 - Neonatal Intensive Care Unit, San Bortolo Hospital, Vicenza, Italy
- 101 - Neonatal Intensive Care Unit, Azienda Ospedaliera of Perugia, Italy
- 102 - Neonatal Intensive Care Unit, Di Venere Hospital, Bari, Italy
- 103 - Neonatal Intensive Care Unit, MBBM Foundation, San Gerardo Hospital, Monza, Italy

104  
105 Infants with a gestational age between 23+0 and 29+6 weeks will be eligible for inclusion. Infants  
106 of twin pregnancies or born after placental and cord abnormalities, major congenital  
107 malformations, hydrops fetalis, and maternal severe compromise at delivery will be excluded.  
108

### 109 **Primary Outcome**

110 The primary outcome of the study is the reduction of incidence of the composite outcome  
111 represented by 3-4 grade IVH, BPD, and mortality in preterm infants assisted at birth with the PCI  
112 in comparison with UCM. The occurrence of the composite outcome will be assessed at 36  
113 weeks’ gestational age.  
114

### 115 **Secondary Outcomes**

116

117 Secondary outcome measurements include the following:

118 1) 3-4 grade IVH

119 2) BPD

120 3) Mortality

121 Other secondary collected data will be:

122 1) Need for mechanical ventilation in the first 24 h of life

123 2) Peak hemoglobin level and hematocrit in the first 24 h of life

124 3) Need and number of blood transfusions

125 4) Need and duration of non invasive and invasive respiratory support

126 5) Use of inotropic drugs in the first 24 hours of life,

127 6) Cerebral oxygenation in the first 24 hours,

128 7) Superior vena cava blood flow in the first 24 hours.

129

### 130 **Further collected data**

131 The following data will be recorded for each infant: gestational age; birth weight; sex; mode of  
132 delivery; Apgar score at 1 and 5 min; main maternal pathologies; antenatal steroid treatment;  
133 maternal analgesia/anesthesia; highest FiO2 in the delivery room; need for resuscitation  
134 procedures at birth (positive pressure ventilation, intubation, chest compressions, drugs); body  
135 temperature at admission; hemoglobin and hematocrit maximum values in the first 24 hours; the  
136 highest FiO2 and mean airway pressure (MAP) values; need and duration of non-invasive  
137 (NCPAP, biphasic positive airway pressure, nasal intermittent mandatory ventilation), and  
138 invasive (patient-triggered ventilation or high frequency oscillatory ventilation) respiratory support;  
139 and need and duration of nitric oxide therapy. We will also report the occurrence of patent ductus  
140 arteriosus (PDA) requiring pharmacological or surgical treatment, of IVH, periventricular  
141 leukomalacia (PVL), NEC, ROP, and hospital stay duration.

142 A diagnosis of sepsis will be based on clinical and laboratory data (white cell count, C-reactive  
143 protein concentration) and will be confirmed by positive blood cultures (9). IVH will be graded  
144 according to a standard classification system (10). A diagnosis of PVL will be made when cystic  
145 areas are detected by cerebral ultrasonography at 40 weeks post-conception birth (11). BDP will  
146 be diagnosed according to the definition by Jobe and Bancalari (12). ROP will be graded  
147 according to the international classification of retinopathy of prematurity (13). NEC will be  
148 diagnosed in agreement with classical Bell's criteria (14).

149

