## 248 **Participant timeline**

249 The patients enrolled in the trial do not receive extra laboratory tests. A heart ultrasound is  
250 performed in the first 24 hours of life and then repeated until PDA closure or as needed. The  
251 direction of ductal shunt, right and left ventricular stroke volume, and superior vena cava flow are  
252 recorded at the first heart ultrasound. All echographic studies are performed in participating centers  
253 by pediatric cardiologists or by neonatologists trained and certified for neonatal echocardiography,  
254 fulfilling the current recommendations for echocardiography training in the NICU (19).  
255 Serial cerebral ultrasounds for evidence of possible IVH and/or PVL are performed in the first 24  
256 hours of life, at 2, 3, 6, 7 (±1), 15 (±2), and 30 (±2) days of life, and at 40 weeks post-conception.  
257 We will collect severe IVH but also Grade 1 and 2 IVH. We will consider only local reads.  
258 Cerebral oxygenation monitoring by near infrared spectroscopy is performed as soon as possible  
259 after the admission of the newborn in NICU and last 24 hours.

260

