### 319 **Data collection methods**

320 All collected data will be obtained from the clinical records. Data collection forms are included in  
321 the electronic case report form (eCRF) that was specifically designed for the trial using a not  
322 validated web-based proprietary application that is compliant with the European regulations  
323 regarding electronic records and signatures. Subjects are identified by sex, birth date, and  
324 assigned trial number only, in accordance with personal data protection law. The study  
325 coordinator and trial statistician will review the generated results for logic, coherence, or  
326 problems. Outlier data will be investigated.

327 Once an infant is enrolled or randomized, the study site will make every reasonable effort to  
328 follow the infant for the entire study period.

329

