## 4 ENDPOINTS AND COVARIATES

### 4.1 EFFICACY VARIABLES

#### 4.1.1 Primary efficacy variable

The primary efficacy variable is a composite endpoint that consists of grade 3-4 IVH, moderate/severe BPD, and death at 36 weeks of post-conceptional age.

IVH and BPD were diagnosed following the criteria of Papile (19) and Jobe and Bancalari (20), respectively.

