|                                | Arm A         |   | Arm B |   |       |   |
|                                | N             | % | N     | % | N     | % |
| Pharmacological closure of PDA |               |   |       |   |       |   |
| No                             |               |   |       |   |       |   |
| Yes                            |               |   |       |   |       |   |
| Missing value                  |               |   |       |   |       |   |
| Total                          |               |   |       |   |       |   |

NOTE: Arm A = UMBELICAL CORD MILKING, Arm B = DELAYED UMBELICAL CORD CLAMPING

TABLE 6.13: DISTRIBUTION OF PATIENTS BY NECROTIZING ENTEROCOLITIS AND TREATMENT ARM (1)

*SAFETY POPULATION*

|               | Treatment Arm |   |       |   | Total |   |
|---------------|---------------|---|-------|---|-------|---|
|               | Arm A         |   | Arm B |   |       |   |
|               | N             | % | N     | % | N     | % |
| NEC           |               |   |       |   |       |   |
| No            |               |   |       |   |       |   |
| Yes           |               |   |       |   |       |   |
| Missing value |               |   |       |   |       |   |
| Total         |               |   |       |   |       |   |

NOTE: Arm A = UMBELICAL CORD MILKING, Arm B = DELAYED UMBELICAL CORD CLAMPING

TABLE 6.14: DISTRIBUTION OF PATIENTS BY PERIVENTRICULAR LEUKOMALACIA AND TREATMENT ARM (1)

*SAFETY POPULATION*

|               | Treatment Arm |   |       |   | Total |   |
|---------------|---------------|---|-------|---|-------|---|
|               | Arm A         |   | Arm B |   |       |   |
|               | N             | % | N     | % | N     | % |
| PLV           |               |   |       |   |       |   |
| No            |               |   |       |   |       |   |
| Yes           |               |   |       |   |       |   |
| Missing value |               |   |       |   |       |   |
| Total         |               |   |       |   |       |   |

NOTE: Arm A = UMBELICAL CORD MILKING, Arm B = DELAYED UMBELICAL CORD CLAMPING

TABLE 6.15: DISTRIBUTION OF PATIENTS BY INTRAVENTRICULAR HEMORRHAGE AND TREATMENT ARM (1)

*SAFETY POPULATION*

|               | Treatment Arm |   |       |   | Total |   |
|---------------|---------------|---|-------|---|-------|---|
|               | Arm A         |   | Arm B |   |       |   |
|               | N             | % | N     | % | N     | % |

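### PVL is tied to the 40-week ultrasound although earlier scans also look for it, so the PVL safety comparison depends on surviving to, and being scanned at, 40 weeks

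*Combined protocol and SAP*

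**What the plan says.** The only PVL case definition in either document is in the protocol, Further collected data: "A diagnosis of PVL will be made when cystic" "areas are detected by cerebral ultrasonography at 40 weeks post-conception birth".

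The protocol's Participant timeline gives the purpose and dates of the scans: "Serial cerebral ultrasounds for evidence of possible IVH and/or PVL are performed in the first 24" "hours of life, at 2, 3, 6, 7 (±1), 15 (±2), and 30 (±2) days of life, and at 40 weeks post-conception". That is eight time points, and all of them serve both diagnoses.

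SAP 4.2 lists the incidence of PVL (abbreviated PLV there) as a safety variable, with no definition and no time point. The planned display is "TABLE 6.14: DISTRIBUTION OF PATIENTS BY PERIVENTRICULAR LEUKOMALACIA AND TREATMENT ARM (1"), on the safety population, with rows for No, Yes and Missing value.

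Three SAP rules fix how that table is filled:
- SAP 5.2.4 analyses safety variables in the same way as the other secondary efficacy variables.
- SAP 5.2.3 calculates percentages over all infants in the arm and in the analysis population.
- SAP 4.3 keeps infants with a missing value in the population, as a category of their own.

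On the source of the data, the protocol (Data collection methods) says: "All collected data will be obtained from the clinical records".

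**The concern.** A case definition that names one scan, with no provision for earlier ones, is met at that scan. Yet the plan obtains earlier scans for the same diagnosis. It does not say whether cysts seen on day 15 or day 30 count as PVL, nor how to code an infant who has no 40-week scan. Two centres could code the same day-30 finding differently.

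If the definition is applied literally, a positive finding in an infant who later dies or is lost before 40 weeks is never counted. The PVL percentage then mixes two things: how often cysts occur, and how often infants live to and attend the last scan. Lower mortality is one of the effects the trial hypothesises (SAP 2.2), so survival may differ between arms. An arm with better survival would have more infants able to become a Yes, which could distort a between-arm PVL comparison in either direction.

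**Working it through.** **1. The provisions side by side**

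| Place | What it settles | What it leaves open |
|---|---|---|
| Protocol, Further collected data | Cystic areas at 40 weeks make the diagnosis | Whether earlier cysts count |
| Protocol, Participant timeline | All eight scans look for IVH and/or PVL | What a positive earlier scan does to PVL status |
| SAP 4.2 | PVL incidence is a safety variable | Definition and time point |
| SAP Table 6.14 | No / Yes / Missing value | Coding of deaths and absent 40-week scans |
| SAP 4.3, 5.2.3, 5.2.4 | Missing infants stay in the denominator | – |

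**2. One infant traced through the rules.** Suppose cysts are seen on day 30, the infant dies before 40 weeks, and the infant received one of the two study procedures. The infant belongs to the safety population (SAP 3.4). The protocol definition is not met, so the entry cannot be Yes. The documents do not say whether it becomes No or Missing value. In both cases the infant remains in the denominator (SAP 4.3, 5.2.3). An infant who survives but has no 40-week scan follows the same path. This needs no assumption about cysts resolving.

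**3. The unscanned interval.** Births are at 23+0 to 29+6 weeks and the day-30 scan has a window of ±2 days.
- Earliest: 23+0 weeks + 28 days = 27+0 weeks.
- Latest: 29+6 weeks + 32 days = 34+3 weeks.
- Gap from day 30 to 40 weeks: 40 − (23 + 30/7) = 12.7 weeks, down to 40 − (29 + 6/7 + 30/7) = 5.9 weeks.

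So about 6 to 13 weeks pass with no scheduled scan.

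**4. The plan's own figure.** There is no stated PVL figure to reproduce. The base of 106 per arm is the protocol's sample size for the composite (47% v 28%, two-sided 0.05, 80% power, 5% dropout):

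n = [1.960 × √(2 × 0.375 × 0.625) + 0.842 × √(0.47 × 0.53 + 0.28 × 0.72)]² / 0.19² = 100.7; 100.7 / 0.95 = 106.0.

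The 106 is reproduced.

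**5. Infants whom death removes from the qualifying scan.** Mortality in the participating units is 14.6% (protocol, Sample Size Calculation).
- 106 × 0.146 = 15.5 per arm; 212 × 0.146 = 31.0 in total.
- With the SAP's 100 per group (SAP 2.7): 100 × 0.146 = 14.6.

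Either way this is about 15 per arm. It assumes the same rate in both arms, every death before 40 weeks, and everyone in the safety population.

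**6. Dependence on survival, as illustration only.** The protocol cites a 32% reduction in mortality for delayed against immediate clamping, which is not this trial's comparison. If it applied here, deaths would be 15.5 × 0.68 = 10.5 against 15.5. About 5 more infants in one arm could then reach the only qualifying scan.

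**7. What cannot be computed.** The documents give no PVL rate, no share of cysts seen early but absent at 40 weeks, and no share of survivors without a 40-week scan. The number of missed cases therefore has no documentary basis.

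**The case against.** The strongest reply is that no exclusion is written. The definition does not say that earlier cysts are disregarded, and the timeline says that the earlier scans look for PVL too. A single assessment age is also a defensible rule. The 40-week scan is scheduled, sites undertake to follow infants as far as they reasonably can, and missing values would appear by arm in Table 6.14.

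This stands in part. Exclusion of earlier cysts is the natural reading but not the stated text, so the fault is an unreconciled definition. The Missing value row shows how many infants are unclassified, but not how many of them had cysts on an earlier scan.

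Three stronger readings are tempting and not supported:
- **A conflict with the 36-week endpoint.** A reader might infer a fault because the protocol says of the composite "The occurrence of the composite outcome will be assessed at 36" weeks. PVL is not a component: "The primary efficacy variable is a composite endpoint that consists of grade 3-4 IVH, moderate/severe BPD, and death at 36 weeks of post-conceptional age". Assessing a separate safety variable four weeks later is not an inconsistency.
- **Proven under-ascertainment, or a proven difference between arms.** Loss of cysts by term and discharge before 40 weeks are not documented, and nothing shows that 40-week scanning differs by arm.
- **Reading the 15 per arm as lost PVL cases.** It counts infants who could not have the scan. An infant who dies before day 15 has neither later scan under any definition, so the fix would recover fewer.

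The stakes are also modest. PVL is one of 17 safety variables in SAP 4.2. Under assumed PVL rates of 2% to 10%, power to detect a halving with 106 per arm is only about 9% to 28% even with no cases missed.

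**Conclusion.** The concern holds as a minor correction to a safety variable. The PVL definition, the scan schedule and the SAP table do not agree on which scans count. Under the definition as written, a known positive earlier scan is lost when the infant dies or is not scanned at 40 weeks, while the infant stays in the denominator.

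The only part the documents let us size is death: at most about 15 of 106 infants per arm, on the assumptions in step 5. Absent scans among survivors would add to this by an unknown number. No sample size, error rate or primary result changes.

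**What to change.** Before database lock, and without reference to PVL results by arm:

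1. In the protocol (Further collected data) and SAP 4.2, define PVL as cystic areas on any scheduled cerebral ultrasound up to and including 40 weeks post-conception.
2. Use this ever-detected status in Table 6.14.
3. Add a separate display of the 40-week finding among infants scanned at that age.
4. Code as missing only infants without an evaluable scan for PVL, and state which scans make an infant evaluable. Show by arm how many died before 40 weeks or had no 40-week scan.

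Cost: a wording change in two places and one extra display, with no new scans. Some transient early findings may be counted, which the separate 40-week display makes visible. The documents do not show that the eCRF holds PVL results scan by scan, so earlier results may have to be retrieved from clinical records. SAP 2.4 reports enrolment as complete, so the change should be recorded as made after recruitment.
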